## Methods/design

### Primary research question

The primary research question is: in mothers of preterm infants 23–29 completed weeks (23 1/7-29 6/7 weeks) gestation at birth who are pumping to provide expressed breast milk for their infant(s) and are identified as having an inadequate milk supply, does the administration of domperidone compare to placebo increase breast milk volume without any signs of harm over a 2 week period?

### Secondary research questions

There are several secondary research questions:

i. Is there a relationship between the volume of breast milk produced and timing of initiation and duration of domperidone to treat mothers with defined low breast milk supply?

ii. Does gestation at birth contribute to any treatment effect from domperidone in mothers with defined low breast milk supply?

iii. Is there a difference in the volume of breast milk produced in mothers identified having an inadequate supply within 7–14 days post delivery versus mothers identified 15–21 days post delivery?

iv. Is there a difference in the use of supplementation such as donor breast milk or preterm infant formula between the different strategies of administration during the study period?

v. Is there a difference in the use of supplementation, such as formula or donor breast milk by the mother to her infant at 40 weeks post conceptual age (term) and at 6 weeks corrected age (6 weeks post term) between the two groups?

vi. Is there a difference in potential adverse events or effects, in particular, those related to gastrointestinal or cardiac difficulties between the two approaches?

### Design

EMPOWER is a multi-centre, double-masked, randomized controlled trial in which 560 mothers will randomized to one of two allocated groups: **Group A**: domperidone 10 mg orally three times daily for 28 days; and **Group B**: identical placebo 10 mg orally three times daily for 14 days followed by domperidone 10 mg orally three times daily for 14 days. (Figure
1) The primary outcome will be determined at the completion of the **first 2-week period** comparing study drug and placebo; the second 2-week period will facilitate answering the secondary questions regarding timing and duration of treatment. The mothers will be contacted when their infants are term gestation (40 weeks post conceptual age) and 6 weeks corrected (6 weeks post date of confinement) to document the feeding patterns (breastfeeding/bottle feeding), continued frequency of breast stimulation, additional use of a galactogogue or alternative after the study period, and the use of supplementation other than mother’s own milk for their infants at these time points. In addition, the mothers will be asked to a few questions regarding the intervention and their participation in the trial.

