### Rationale for phase II trial

Mothers of preterm infants are at a higher risk of a decline in milk production. It has been recommended that they should be evaluated no later than two weeks postpartum to determine what intervention may be required to assist them in augmenting and maintaining an adequate supply of milk
[24]. Although other measures can and should be considered, the use of a galactogogue often becomes the measure of choice, particularly when the other techniques are unsuccessful. The limited body of research on domperidone suggests that it has potential as a galactogogue in mothers of preterm infants; this has led to widespread use of this medication. However, there is a paucity of research to best guide clinicians as to the optimal dose, timing of administration and duration of treatment and to reaffirm safety. EMPOWER was initiated to firmly establish the safety of domperidone for mothers of preterm infants but also guide clinicians regarding initiation, timing and duration of treatment.

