### Randomization

Upon consent, the site co-ordinator will be able to randomize the mother using a 24 hour/day web-based randomization service at the data coordinating centre (DCC) at the Centre for Mother, Infant, and Child Research (CMICR) in Toronto. A treatment number will be issued which will correspond to the study medication at the centre which has been previously sent to the site. The study allocation will be randomly assigned in a 1:1 ratio in blocks of 4 and 8. The study participants will be stratified by centre, gestational age groupings (23–26 and 27–29 weeks gestation at delivery) and days post delivery (7–14 and 15–21 days post delivery).

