#### Secondary outcomes

The secondary outcomes include:

i. mean difference in the tabulated volume in breast milk recorded between the two groups at 2 and 4 weeks (mean day 14 or 28 volume- mean day 0 volume at entry)

ii. mean within-subject differences between the two groups at 2 and 4 weeks (mean day 14 or 28 volume- mean day 0 volume at entry)

iii. effect of gestational age at the time of delivery on the volume of milk (23–26 and 27–29 weeks gestation at delivery) between the two groups

iv. effect of timing of inadequate milk supply post delivery on the volume of milk (7–14 and 15–21 days) between the two groups

v. difference in the use of supplementation to expressed breast milk, such as formula or donor breast milk between the two groups during the study period (day 14 and 28)

vi. rates of breastfeeding, use of supplementation, such as formula or donor breast milk at 40 weeks post conceptual age (term) and at 6 weeks post term between the different groups

vii. potential differences in adverse events, in particular, those related to gastrointestinal or cardiac difficulties

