### Statistical analysis

All analyses will be carried out using SAS Version 9.1 (SAS Institute, Cary, NC, USA). Descriptive statistics will be calculated for all variables of interest. Continuous measures will be summarized using means and standard deviations whereas categorical measures will be summarized using counts and percentages.

The primary outcome will be assessed between groups using a logistic regression model. This model will account for correlation among observations taken at the same centre as well as multiple births by the same mother using generalized estimating equations. The model will take into account variables such as gestational age and days post delivery. The number of variables included in the model will be determined using regression modeling guidelines (i.e. for logistic models, the maximum number of variables allowed will equal the number of observations in the smallest of the two outcome categories divided by 10). Prior to analysis, variables will be assessed for the presence of multi-collinearity (tolerance statistic < 0.4), and in this case, only one member of a correlated set will be retained in the model.

The secondary outcomes involving mean difference in the tabulated volume in breast milk will be assessed using a repeated measure analysis of covariance comparing the different groups across the time points of interest, adjusting for correlation among observations taken at the same centre and on the same subject. The model will assess differences between groups, differences over time (within-subject differences), and the group by time interaction adjusting for gestational age and days post delivery.

A linear regression model will be run to assess the relationship between gestational ages at time of delivery on the volume of milk. The model will include group, gestational age (23–26 weeks, or 27–29 weeks), as well as the group by age interaction term. Another linear regression model will be run to assess the relationship between timing of inadequate milk supply post delivery on the volume of milk. The model will include group, timing (7–14 days, 15–21 days), as well as the group by timing interaction term. All regression models conducted in this study will be run using likelihood based methods to account for missing data. The models will also treat twins or triplets as a correlated set of data to adjust for their dependent nature.

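### At day 28 the two arms differ in start time and duration together, so the second period can compare two strategies but cannot answer timing and duration separately

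*Protocol article*

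**What the plan says.** The protocol article (Design) sets two arms. Group A receives "domperidone 10 mg orally three times daily for 28 days". Group B receives "placebo 10 mg orally three times daily for 14 days followed by domperidone 10 mg orally three times daily for 14 days". Under Randomization, "The study allocation will be randomly assigned in a 1:1 ratio in blocks of 4 and 8". No third arm is described.

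Three places present timing and duration as things the trial will inform:

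- Rationale for phase II trial: the trial was started partly to "guide clinicians regarding initiation, timing and duration of treatment".
- Secondary research questions, item i: "Is there a relationship between the volume of breast milk produced and timing of initiation and duration of domperidone".
- Design, repeated in the Abstract: "the second 2-week period will facilitate answering the secondary questions regarding timing and duration of treatment".

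Secondary outcomes, item i, is the "mean difference in the tabulated volume in breast milk recorded between the two groups at 2 and 4 weeks". Statistical analysis assigns the volume outcomes to a repeated-measures analysis of covariance: "The model will assess differences between groups, differences over time (within-subject differences), and the group by time interaction". A separate linear model contains group, days post delivery at entry (7–14 or 15–21) and their interaction.

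**The concern.** Group A starts 14 days earlier than group B and also takes the drug for 14 days longer. No arm combines an early start with 14 days of treatment, or a late start with 28 days. A reader of secondary question i would expect to learn whether starting earlier matters and whether treating longer matters. The two arms can supply only one number at day 28, in which both influences are combined. The stake is that clinicians could be given separate guidance on timing and on duration that the data cannot contain.

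A related, lesser issue arises in the volume model. Group B is on active drug by day 28, so a group effect taken over both visits mixes a placebo-controlled comparison with a comparison of two active strategies. It is not the effect of domperidone at either visit unless the day-28 and day-14 differences happen to be equal.

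**Working it through.** **1. The plan's own figure.** The only stated sample size (Abstract) is for the day-14 responder outcome: 40% versus 28%, 80% power, alpha 0.05, 488 mothers. With two-sided alpha and pooled variance under the null (mean proportion 0.34):

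n per arm = [1.96·√(2·0.34·0.66) + 0.8416·√(0.40·0.60 + 0.28·0.72)]² / 0.12² = [1.313 + 0.559]² / 0.0144 ≈ 243.4, so 244 per arm and 488 in total.

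The figure reproduces. No calculation is stated for the timing and duration questions.

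**2. What the four arm-by-visit means can identify.** Define:

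- m14, m28: mean volume without drug at days 14 and 28
- e: effect of 14 days of drug started at day 0
- T: change in that effect if the same 14 days start at day 14
- D: change in that effect if treatment from day 0 lasts 28 days instead of 14

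The means are:

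| | Day 14 | Day 28 |
|---|---|---|
| Group A | m14 + e | m28 + e + D |
| Group B | m14 | m28 + e + T |

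There are four means and five unknowns, and the design matrix has rank 4. The contrasts are:

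- A − B at day 14 = e. This is estimable and is the placebo-controlled effect.
- A − B at day 28 = D − T. Only this difference is estimable.
- B at day 28 − A at day 14 = (m28 − m14) + T. Duration is matched at 14 days, but the time trend is mixed in.
- A at day 28 − A at day 14 = (m28 − m14) + D. The same trend is mixed in.

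Adding a constant to T and to D, and subtracting it from m28, leaves all four means unchanged. Neither T nor D can therefore be recovered from any analysis of these means. A zero difference at day 28 fits T = D = 0, and equally fits T and D that are non-zero and equal. Purely as an algebraic check, an untreated mean at day 28 would raise the rank to 5; the design has none.

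**3. The overall group effect.** Let r be the day-28 group difference divided by the day-14 difference. With equal weight on the two visits, the overall group effect is (1+r)/2 of the day-14 effect:

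- r = 0 (group B fully catches up): 50%
- r = 0.5: 75%
- r = 1 (all of the difference persists): 100%

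**4. Illustrative power.** The article gives no standard deviation for volume, no correlation between visits and no expected day-28 effect. Assumptions: 244 per arm, equal SD at both visits, a day-14 contrast with exactly 80% power, and a visit correlation ρ of 0.3 to 0.7. The day-14 effect is then (1.96 + 0.8416)·√(2/244) = 0.254 SD. The average of two visits has SD √((1+ρ)/2), so

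power = Φ( 2.8016·[(1+r)/2] / √((1+ρ)/2) − 1.96 ).

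| r | ρ = 0.3 | ρ = 0.5 | ρ = 0.7 |
|---|---|---|---|
| 0 | 41% | 37% | 33% |
| 0.5 | 74% | 68% | 63% |
| 1 | 94% | 90% | 86% |

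The day-14 contrast has 80% in every cell by construction. The overall effect has lower power when group B catches up, and higher power when the difference persists.

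**The case against.** **On timing and duration.** The article never says outright that two separate effects will be estimated. Question i asks about a relationship, which can be read jointly, and the Design section only says that the second period helps. Elsewhere among the secondary questions (items iv and vi) the arms are already treated as strategies or approaches, and the 4-week volume outcome is simply a difference between groups. Timing also has its own route: stratification by days post delivery and a group-by-timing interaction.

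Part of this stands. The day-28 comparison as defined is already a strategy comparison, and the strata do show whether the placebo-controlled effect varies with time of entry. But mothers are not randomised to a stratum, so such a difference may reflect who is identified late. That analysis does not need the second period, and it is silent on duration. The Rationale and question i still name timing and duration as targets.

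**On the model.** The group-by-time term is specified and the volume outcomes are defined at 2 and 4 weeks, so visit-specific contrasts are available. Which contrast to report is often settled in a statistical analysis plan, which is not shown here. This stands. The model is not wrong, and the article does not state that the overall group effect will be presented as the drug effect. Only that overall test is affected.

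**A stronger reading.** A reader might infer that the volume analysis is bound to understate the drug effect and lose about half its power. For example, converting 40% versus 28% to a normal-scale shift of 0.33 SD, with correlation 0.7 and complete catch-up, gives 51% power for the overall effect against 95% at day 14. The documents do not support this as a finding. They give none of those inputs, and a responder-rate difference does not translate directly into a difference in volume. The same formula gives about 62% at correlation 0.3 with full catch-up. At correlation 0.7 it gives about 84% if half the difference remains and 98% if all of it does.

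**Conclusion.** The point holds in two parts of unequal weight.

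The main part needs no numerical assumption. With these two arms, start time and duration are completely confounded at day 28, and neither more mothers nor another model would separate them. Secondary question i and the matching statements in the Rationale and Design sections suggest more than the second period can deliver.

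The lesser part is that the overall group effect in the repeated-measures model should not be interpreted, because it lies at 50% to 100% of the day-14 effect for r between 0 and 1. Whether this costs power is unknown. Under the stated assumptions the overall effect has about 33–41% power at r = 0, 63–74% at r = 0.5 and 86–94% at r = 1, so no single loss can be claimed.

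It would be wrong to infer that the trial's main result is at risk. The day-14 primary comparison is placebo-controlled and untouched, and the day-28 contrast is a sound randomised comparison of two strategies. The change should be made because it corrects what the trial can conclude at almost no cost.

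**What to change.** 1. Restate secondary question i and the day-28 volume outcome as one randomised strategy comparison: immediate 28-day domperidone versus 14-day domperidone delayed by 14 days. Make no separate claim for timing or for duration, and bring the Rationale and Design wording into line.
2. Describe the days-post-delivery analysis as effect modification by time of entry, not as a randomised test of timing.
3. In the repeated-measures model, name the day-14 contrast as the only drug-versus-placebo estimate of volume and the day-28 contrast as the strategy effect. Take both from the group-by-time terms already specified, and do not test or interpret the overall group effect.

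No change to arms, sample size, treatment or data collection is needed. The cost is rewording and a more modest claim on timing and duration.

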**Figure 1 F1:**
[figure not shown]
EMPOWER Schema.

### Randomization

Upon consent, the site co-ordinator will be able to randomize the mother using a 24 hour/day web-based randomization service at the data coordinating centre (DCC) at the Centre for Mother, Infant, and Child Research (CMICR) in Toronto. A treatment number will be issued which will correspond to the study medication at the centre which has been previously sent to the site. The study allocation will be randomly assigned in a 1:1 ratio in blocks of 4 and 8. The study participants will be stratified by centre, gestational age groupings (23–26 and 27–29 weeks gestation at delivery) and days post delivery (7–14 and 15–21 days post delivery).

### Study setting

The study setting is multi-national with approximately 20–25 centres in Canada, Israel, Qatar, and Chile. Enrollment began in June 2012 and is expected to be completed in 36–42 months.

### Ethics, informed consent and safety

Documented approval has been obtained from the Research Ethics Boards/Institutional Review Boards of the participating centres prior to study start. In addition documented approval has been obtained from Health Canada to study domperidone for this off-label indication. The study is also designed to conform to the International Conference on Harmonization of good clinical practice (GCP) guidelines
[25], as well as local regulations and policies as well as with the Declaration of Helsinki. Written informed consent must be obtained from each participant.

There is no interim analysis planned but regular safety reviews are scheduled for every 100 patients recruited at which time all adverse and serious adverse events are reviewed by the Data Safety Monitoring Board (DSMB). The DSMB will also have the right to review any variables that may have an impact on the trial.

### Eligibility

#### Inclusion criteria

The goal is to identify those mothers truly at higher risk of not being able to produce and maintain a supply of breast milk in sufficient quantities for her infant.

i. mothers of a preterm infant born ≤ 29 completed weeks gestation (23 1/7-29 6/7 weeks)

ii. postpartum period of 7–21 days

iii. mechanically pumping an minimum average of 6 times a day in the 4–7 days prior to entry

iv. experiencing inadequate milk supply defined as providing <100% of the average of the daily nutritional intake during the previous 72 hour period prior to entry based on a fluid intake of 150 ml/kg/d or experiencing a clinical reduction of 30% from a peak volume during the previous 72 hour period prior to entry (maternal report). The 30% reduction reported by the mother will be confirmed by lactation support personnel in the NICU. In the case of mothers with twins, the estimated fluid volume to be produced will be based on the weight of the larger twin. Mothers can be identified in the NICU as early as day 4 until day 18 post delivery.

### Exclusion criteria

i. history of known or suspected cardiac dysrhythmias (tachyarrhythmia, Q-Tc prolongation) or currently on an anti-arrhythmic medication

ii. currently experiencing mastitis

iii. previous breast surgery, including augmentation or reduction, nipple piercing

iv. known chronic or debilitating illness, known abnormal liver function, gastric abnormalities (gastrointestinal hemorrhage, blockage or currently treated acid reflux), HIV

v. known to a have prolactin-releasing pituitary tumor

vi. receiving medications known to alter the metabolism and pharmacokinetics of domperidone (eg. oral “azole” antifungals, erythromycin antibiotics, MAO inhibitors) or medications that have dopaminergic or antidopaminergic activity or affect prolactin levels

vii. mother of higher order pregnancies (triplet, or more)

viii. current cigarette smoking (cigarette smoking is known to diminish prolactin levels)

### Duration of study period

The total study period for the study medication is 4 weeks (28 days). The study medication will end prior to 28 days if any one of the following occurs:

i.  if the infant dies during the study period

ii.  mother’s refusal for ongoing participation with the protocol

iii.  if the mother is experiencing any irregular heartbeats (documented by an ECG)

iv.  if the Q-Tc interval in the ECG is > 0.44 sec (based on standard ECG run at 25 mm/sec) for the mother

v.  if the infant is demonstrating an irregular heartbeat or prolonged Q-Tc interval confirmed by ECG; blood for domperidone level will be drawn on the infant only if this occurs.

### Study outcomes

#### Primary outcome

The primary outcome is the difference between the two groups in achieving a 50% increase in breast milk volume at the end of the first 2-week period (mean day 14 volume- mean day 0 volume at entry).

#### Secondary outcomes

The secondary outcomes include:

i. mean difference in the tabulated volume in breast milk recorded between the two groups at 2 and 4 weeks (mean day 14 or 28 volume- mean day 0 volume at entry)

ii. mean within-subject differences between the two groups at 2 and 4 weeks (mean day 14 or 28 volume- mean day 0 volume at entry)

iii. effect of gestational age at the time of delivery on the volume of milk (23–26 and 27–29 weeks gestation at delivery) between the two groups

iv. effect of timing of inadequate milk supply post delivery on the volume of milk (7–14 and 15–21 days) between the two groups

v. difference in the use of supplementation to expressed breast milk, such as formula or donor breast milk between the two groups during the study period (day 14 and 28)

vi. rates of breastfeeding, use of supplementation, such as formula or donor breast milk at 40 weeks post conceptual age (term) and at 6 weeks post term between the different groups

vii. potential differences in adverse events, in particular, those related to gastrointestinal or cardiac difficulties

### Statistical analysis

All analyses will be carried out using SAS Version 9.1 (SAS Institute, Cary, NC, USA). Descriptive statistics will be calculated for all variables of interest. Continuous measures will be summarized using means and standard deviations whereas categorical measures will be summarized using counts and percentages.

The primary outcome will be assessed between groups using a logistic regression model. This model will account for correlation among observations taken at the same centre as well as multiple births by the same mother using generalized estimating equations. The model will take into account variables such as gestational age and days post delivery. The number of variables included in the model will be determined using regression modeling guidelines (i.e. for logistic models, the maximum number of variables allowed will equal the number of observations in the smallest of the two outcome categories divided by 10). Prior to analysis, variables will be assessed for the presence of multi-collinearity (tolerance statistic < 0.4), and in this case, only one member of a correlated set will be retained in the model.

The secondary outcomes involving mean difference in the tabulated volume in breast milk will be assessed using a repeated measure analysis of covariance comparing the different groups across the time points of interest, adjusting for correlation among observations taken at the same centre and on the same subject. The model will assess differences between groups, differences over time (within-subject differences), and the group by time interaction adjusting for gestational age and days post delivery.

A linear regression model will be run to assess the relationship between gestational ages at time of delivery on the volume of milk. The model will include group, gestational age (23–26 weeks, or 27–29 weeks), as well as the group by age interaction term. Another linear regression model will be run to assess the relationship between timing of inadequate milk supply post delivery on the volume of milk. The model will include group, timing (7–14 days, 15–21 days), as well as the group by timing interaction term. All regression models conducted in this study will be run using likelihood based methods to account for missing data. The models will also treat twins or triplets as a correlated set of data to adjust for their dependent nature.

Use of supplementation, rates of breastfeeding, and adverse events will be assessed using a chi-square analysis comparing groups.

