**Methods/design:**

EMPOWER is a multicenter, double masked, randomized controlled phase-II trial to evaluate the safety and effectiveness of domperidone in those mothers identified as having difficulty in breast milk production. Eligible mothers will be randomized to one of two allocated groups: **Group A**: domperidone 10 mg orally three times daily for 28 days; and **Group B**: identical placebo 10 mg orally three times daily for 14 days followed by domperidone 10 mg orally three times daily for 14 days. The primary outcome will be determined at the completion of the **first 2-week period**; the second 2-week period will facilitate answering the secondary questions regarding timing and duration of treatment. To detect an estimated 30% change between the two groups (from 40% to 28%, corresponding to an odds ratio of 0.6), a total sample size of 488 mothers would be required at 80% power and alpha = 0.05. To account for a 15% dropout, this number is increased to 560 (280 per group). The duration of the trial is expected to be 36–40 months.

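### No efficacy model names day 0 milk volume as a covariate, and supplementation and breastfeeding are tested without the randomisation strata: a loss of precision, not of validity

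*Protocol article*

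**What the plan says.** All references are to the protocol article.

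- **Randomization.** "The study participants will be stratified by centre, gestational age groupings" and by days post delivery (two levels each for gestational age and days).
- **Primary outcome.** A responder endpoint: a rise of at least half in milk volume from day 0 to day 14.
- **Primary model (Statistical analysis).** A logistic model fitted by generalized estimating equations (GEE), with within-centre correlation. On covariates: "The model will take into account variables such as gestational age and days post delivery".
- **Mean volume at 2 and 4 weeks.** A repeated-measures analysis of covariance with correlation within centre and subject. It assesses "the group by time interaction adjusting for gestational age and days post delivery".
- **Subgroup regressions on volume.** One has group and gestational-age stratum "as well as the group by age interaction term". The other has the same form with timing of inadequate supply. No further terms are listed.
- **Binary secondary outcomes.** "Use of supplementation, rates of breastfeeding, and adverse events will be assessed using a chi-square analysis comparing groups".

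The same section also limits the number of variables in the model to one per ten observations in the smaller outcome category. It keeps only one member of any set with tolerance below 0.4.

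**The concern.** Day 0 volume is already collected and is likely to be the strongest predictor available. Inclusion criterion iv admits any mother producing less than the infant's full need, or whose volume has fallen 30% from its peak, so entry volumes should vary widely. A 50% rise is easier to reach from a very small volume than from a nearly adequate one.

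Defining the outcome relative to day 0 does not adjust for day 0. With equal variances at both times, the correlation between baseline and change is −√((1 − ρ)/2), where ρ is the baseline/follow-up correlation. That gives −0.50 at ρ = 0.5 and −0.32 at ρ = 0.8. Change therefore still depends on where the mother started, and leaving that dependence in the residual widens the intervals. The group-by-stratum interaction tests, which have the least power, would feel this most.

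The chi-square issue is similar. Stratified randomisation balances the arms within strata. A test that ignores prognostic strata overstates the variance of the difference and becomes conservative.

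**Working it through.** **1. The plan's own figure.** Inputs from the Abstract: "To detect an estimated 30% change between the two groups (from 40% to 28%, corresponding to an odds ratio of 0.6"), and "a total sample size of 488 mothers would be required at 80% power and alpha = 0.05". With the pooled two-sided formula and no continuity correction:

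n per arm = [1.960·√(2 × 0.34 × 0.66) + 0.842·√(0.40 × 0.60 + 0.28 × 0.72)]² / 0.12² = 243.4, rounded up to 244, or 488 in total.

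This matches and uses no covariate gain. With 15% dropout from 560, 476 mothers remain (238 per arm), with power 0.79.

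**2. Assumed inputs.** The article gives no SD, no baseline/follow-up correlation, no prognostic strength and no centre variance. All results below rest on assumed ranges.

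**3. Continuous outcomes.** With equal variances, the residual variance after baseline adjustment is (1 + ρ)/2 of that for an unadjusted change score, and 1 − ρ² of that for unadjusted follow-up volume. An analysis with 80% power before adjustment then has power Φ[(1.960 + 0.842)/√ratio − 1.960]:

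| ρ | Ratio, change | Power | Ratio, raw volume | Power |
|---|---|---|---|---|
| 0.3 | 0.65 | 0.935 | 0.91 | 0.836 |
| 0.5 | 0.75 | 0.899 | 0.75 | 0.899 |
| 0.7 | 0.85 | 0.860 | 0.51 | 0.975 |
| 0.9 | 0.95 | 0.820 | 0.19 | 1.000 |

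Outcomes i and ii are changes from day 0. The subgroup regressions refer only to volume of milk, so either column could apply to them.

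**4. Primary responder outcome.** Two simulations, both at 28% versus 40% responders:

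- *Log-normal volumes, log SD 0.8, 238 per arm.* Unadjusted versus baseline-adjusted power is 0.78 vs 0.87 (ρ = 0.3), 0.78 vs 0.85 (0.5), 0.79 vs 0.83 (0.7) and 0.79 vs 0.82 (0.8). A separate run at ρ = 0.9 gives 0.79 vs 0.80. Gains run from 9 points down to 1.
- *Baseline odds ratio per SD set directly, 244 per arm.* Power is 0.796 vs 0.794 (odds ratio 1.0), 0.808 vs 0.811 (1.25), 0.796 vs 0.807 (1.5), 0.812 vs 0.843 (2.0) and 0.805 vs 0.861 (2.5). Gains run from 0 to about 6 points.

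In the log-normal model, ρ from 0.3 to 0.9 corresponds to odds ratios of 3.5 down to 1.5 per SD, so the two sets agree where they overlap.

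**5. Chi-square versus a stratified Cochran–Mantel–Haenszel (CMH) test.** No rates are given for supplementation or breastfeeding, so 28% and the odds ratio for 28% versus 40% stand in. Four equal strata, 244 per arm:

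| Stratum spread (logit) | Type I error, chi-square / CMH | Power, chi-square / CMH |
|---|---|---|
| 0 | 0.051 / 0.051 | 0.803 / 0.802 |
| ±0.25 | 0.051 / 0.051 | 0.798 / 0.800 |
| ±0.5 | 0.047 / 0.049 | 0.783 / 0.790 |
| ±1.0 | 0.037 / 0.048 | 0.730 / 0.764 |

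With 22 centres and a strong centre effect (logit SD 1.0 to 1.5), chi-square rejects 3.6% to 2.4% of the time under the null. Its power is 71% to 57%, against 77% to 71% for a centre-stratified CMH.

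**6. What the data can carry.** The article's own limit allows 476 × 0.34 ≈ 162 responders, and 162/10 ≈ 16 variables. Baseline volume fits. Fixed centre effects do not: 20 to 25 centres need 19 to 24 indicators, which with group, baseline and two strata makes 23 to 28 terms. A CMH over every randomisation cell would have about 22 × 2 × 2 = 88 cells, with 476/88 ≈ 5 mothers each.

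**The case against.** The strongest reply is that a final covariate list is ordinary analysis-plan content and that this plan is not shown. That holds in part for the primary model, whose list is introduced only by way of example. It does not hold for the subgroup regressions, which list their terms, or for the chi-square tests, which the article fixes outright.

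A reader might infer that baseline is excluded from every efficacy model. The text does not support this. The primary list does not rule baseline out, and day 0 may be one of the repeated-measures time points, which the article does not say. What can be said is that no model names it.

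A reader might also infer that the strata are ignored throughout. They are not. The primary and repeated-measures models take in gestational age and days post delivery as covariates and centre through correlation. The gap is confined to the chi-square tests and, in part, the subgroup regressions.

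It is also fair that the magnitudes are assumed, that strong centre effects produce the larger chi-square figures, and that chance baseline imbalance is already covered by the error rate of a randomised comparison. All of this stands and limits the point to efficiency. It does not remove it, because adjustment uses data already in hand.

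**Conclusion.** The point holds as one of precision and pre-specification. Type I error is not inflated anywhere, and the 488 stands without covariate gain.

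- *Continuous outcomes:* variance falls by 35% to 5% for change scores, or by 9% to 81% for raw follow-up volume, over ρ of 0.3 to 0.9. This could be material, particularly for the interaction tests.
- *Primary outcome:* about 0 to 9 power points, with zero only if baseline volume barely predicts response.
- *Supplementation and breastfeeding:* under 1 point for stratum effects up to ±0.5 logit, about 3 points at ±1.0, and 6 to 14 points only under the strong centre effects assumed above. In those last two cases the chi-square test is conservative.

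The direction of these effects is firm; their size cannot be derived from the article.

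**What to change.** - Pre-specify log day 0 volume, the gestational-age stratum and the days-post-delivery stratum in the primary logistic GEE, the repeated-measures model and both subgroup regressions. Replace the open list with this closed one, and exempt these terms from the collinearity and number-of-variables rules.
- Keep centre handled by within-centre correlation and extend that to the two subgroup regressions. Do not add fixed centre effects.
- For supplementation and breastfeeding, replace the plain chi-square with a logistic GEE adjusted for the two strata and clustered by centre, or with a centre-stratified CMH test. Avoid a CMH over all of the roughly 88 cells.

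The cost is wording, with no new data. The one drawback is that the odds ratio becomes conditional on the covariates, so an adjusted risk difference should be reported beside it.
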